**Fig. 2 Fig2:**
[figure not shown]
X-ray contrast densitometry with the special software (CAAS A‑Valve) after transcatheter aortic valve implantation

Echocardiography, including TTE and TEE, is performed within five days following TAVI. The use of the Doppler technique provides accurate information on the number and severity of paravalvular jets. In addition, 3D TEE is used to analyse the complete morphology of the PPR colour flow stream in the region of its origin. Consequently, views from any level can be obtained, and the direction and extension of PPR jets can be assessed. New dedicated analysis software (Personal Space Technologies BV, the Netherlands) designed for the visualisation and analysis of 3D volumetric echocardiography data will be used for the quantitative grading of PPR severity in this study.

Patients will undergo cerebral MRI including a diffusion-weighted imaging sequence on day 4 (+1) after TAVI, for detection of new cerebral ischaemic injury [30]. In order to detect kidney injury related to TAVI, serum and urine samples (including 24-hour urine) will be collected. Acute kidney injury will be assessed within 5 days after TAVI and compared with baseline. Irreversible kidney injury (VARC-2) will be assessed at 6‑month follow-up. In order to investigate possible mid-term changes in post-TAVI PPR, valvular function will be evaluated at 6 months using TTE and 3D TEE as described above. Finally, validated quality of life questionnaires (KCC-Q, EuroQol EQ-5D and SF-36) will be used to measure health-related quality of life at one year follow-up and compared with baseline (Fig. 3).

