## Statistical analysis

Descriptive statistics will be used to ascertain any imbalance between the arms at baseline. The extent of missing data will be reported and baseline factors will be compared for completers and non-completers to assess the extent of any bias that may result.

Continuous variables are presented as means ± standard deviation or medians [interquartile range], as considered appropriate, and categorical variables as counts and percentages. Continuous variables will be compared using the Student *t* test or Mann-Whitney test, depending on data distribution. Categorical variables will be compared using chi-square or Fisher’s exact test, as considered appropriate. For the analysis of the difference in PPR between each of the prostheses, log transformation will be performed on the regurgitation volume data before performing a *t* test, as these data are expected to be right-skewed. The follow-up analysis for changes in the endpoints in the time within the arms will be performed using the paired *t* test and the repeated measurements analysis of variance. A two-tailed *p*-value of less than 0.05 is regarded as statistically significant. All analyses will be performed according to the intention-to-treat principle. Data will be analysed using IBM SPSS Statistics software version 20 (IBM Corp., Armonk, NY, USA), and R version 2.12.0 (http://www.r-project.org).

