Interestingly, the recently published results of the CoreValve US Pivotal Trial [32] showed that the incidence of any PPR after the implantation of CV-THV decreases over time: 41.1% at discharge and 31.9% at one year. The latter was also accompanied by a reduction in the incidence of more-than-mild aortic regurgitation during follow-up, at 13.8% at discharge, 10.1% at 6 months, and 6.4% at one year. This suggests that measurement of post-TAVI PPR in the CV-THV during the few first days after TAVI will probably overestimate its long-term severity. In the ELECT study, the severity of PPR is also measured at 6‑month follow-up using transthoracic and 3D transoesophageal echocardiography, which allows for a more reliable comparison between the two prostheses.

One previously published meta-analysis [25] showed a higher risk of moderate or severe post-procedural PPR after CV-THV implantation (16%) as compared with E﻿d﻿w﻿a﻿r﻿d﻿s SAPIEN implantation (9.1%, *p* = 0.005). The CHOICE study [18], which is the only randomised head-to-head trial to date that has compared the balloon-expandable SXT-THV with the CV-THV system, reported a significant difference in the frequency of any degree of PPR (38% in SXT group versus 65% in the CV group, *p* < 0.001) and more-than-mild PPR (4.1% in SXT group versus 18.3% in the CV group, *p* < 0.001 by angiography) favouring the balloon-expandable valve. However, the extent of the PPR in the CHOICE trial was measured using aortic root angiography immediately after prosthesis implantation, which is an important limitation of this clinical trial.

On the other hand, the PRAGMATIC [33] study reported a very low and comparable incidence of more-than-mild PPR with both Edwards SAPIEN and CV-THV (1.8% and 2.0%, respectively) in a large multicentre propensity score-matched study. Recently, another study among a selected group of patients receiving S3-THV or CV-THV reported a significantly lower rate of mild or severe PPR, lower need for permanent pacemaker implantation, and higher rate of device success for the S3-THV compared with CV-THV. However, this study was limited by its design and small sample size [34].

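### The only analysis stated for change over time is within each arm, so it cannot test whether PPR or quality of life changes differently between the two devices

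*Protocol article*

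**What the plan says.** The Statistical analysis section of the protocol article contains three relevant statements.

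- Between groups, in general: "Continuous variables will be compared using the Student" t or Mann-Whitney test, and "Categorical variables will be compared using chi-square or Fisher’s exact test, as considered appropriate". No endpoint or visit is named.
- Between groups, for leakage: "For the analysis of the difference in PPR between each of the prostheses, log transformation will be performed on the regurgitation volume data", followed by a t test. Again no visit or imaging modality is named.
- Change over time: "The follow-up analysis for changes in the endpoints in the time within the arms will be performed using the paired" t test and repeated-measures ANOVA.

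The Secondary endpoints section sets the visits. Echocardiography is done within five days of TAVI and repeated later: "In order to investigate possible mid-term changes in post-TAVI PPR, valvular function will be evaluated at 6 months using TTE and 3D TEE". The quality-of-life questionnaires "will be used to measure health-related quality of life at one year follow-up and compared with baseline".

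The Discussion says that early measurement in CoreValve patients "will probably overestimate its long-term severity", because the self-expanding frame may seal better as time passes. It then says that PPR is also measured by echocardiography at 6 months, "which allows for a more reliable comparison between the two prostheses". The last paragraph of the Abstract gives differences between the prostheses in mid-term outcome and quality of life as an aim.

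**The concern.** The Discussion raises a question about differential change: does leakage fall more after CoreValve than after SAPIEN-3? The only method tied to change asks something else, namely whether each arm, taken alone, moved from its own starting level. Those p-values are before-after results and do not use the randomisation.

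What is at stake is the reading of the 6-month PPR and one-year quality-of-life results. If the within-arm tests are what is reported on change, a result that is significant in one arm and not in the other invites a conclusion about the devices that has not been tested.

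**Working it through.** **Inputs.** Two-sided alpha 0.05, 49 per arm after dropout and 54 randomised per arm (Statistical analysis; Sample size calculation). Log-scale planning values from the same section: means 0.32 and 0.63, SD 0.53. The SD of change and the within-arm power are not given. Within-arm powers of 30%, 50% and 80% are assumptions that show the range.

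**The plan's own figure.** The planned difference is 0.63 − 0.32 = 0.31. The normal formula gives n = 2 × [0.53 × (1.960 + 0.842) / 0.31]² = 45.9, so 46 per arm. The exact t test gives 47. The stated 49 is close to this and has about 82% power. It concerns the primary CMR comparison, is not in dispute, and serves below only as the number per arm.

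**Which hypothesis each method tests.** Let Δ_S and Δ_C be the mean changes with SAPIEN-3 and CoreValve.

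- Paired tests within arms: Δ_S = 0 and, separately, Δ_C = 0.
- Two-sample test of follow-up values: equal means at that visit.
- The question in the Discussion: Δ_C − Δ_S = 0.

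The follow-up difference equals the early difference plus (Δ_C − Δ_S). For PPR the early difference is not expected to be zero, since the trial is powered for 0.31 on the log scale by CMR. The 6-month difference and the differential change are therefore separate questions, and both matter. For quality of life the baseline precedes implantation, so randomisation makes the expected baseline difference zero. A two-sample test at one year then has the right target. What it loses is precision and protection against chance imbalance: adjustment for baseline multiplies the residual variance by about 1 − ρ², where ρ is the baseline to one-year correlation (not given).

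**Does repeated-measures ANOVA supply the missing contrast?** The text describes two echocardiographic time points and two quality-of-life time points. With two time points, a within-arm repeated-measures ANOVA is the paired t test (F = t²). It could supply the contrast only with an arm factor, and the wording places it within the arms.

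**Size of the error if within-arm results were compared informally.** The arms are independent. With equal true change and within-arm power p, exactly one arm is significant with probability 2p(1 − p):

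- p = 0.30: 2 × 0.30 × 0.70 = 0.42
- p = 0.50: 2 × 0.50 × 0.50 = 0.50
- p = 0.80: 2 × 0.80 × 0.20 = 0.32

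A simulation (20,000 trials, 49 per arm, normal change scores, equal true change) agrees:

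| True change in each arm (SD of change) | Exactly one arm significant | Between-arm t test on change significant |
|---|---|---|
| 0 | 9.1% | 4.8% |
| 0.21 (power about 30%) | 42.6% | 4.9% |
| 0.286 (power about 50%) | 50.3% | 5.1% |
| 0.41 (power about 80%) | 31.4% | 5.0% |

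**What a between-arm test could detect.** With 80% power, a difference in change of 0.57 SD at 49 per arm, or 0.60 SD at 44 per arm (assuming about 10% further loss). Without the SD of change this cannot be put in ml or questionnaire points.

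**The case against.** The strongest reply is that the section already has between-group tests. The general two-sample tests and the log-volume t test between prostheses are not confined to the early visit, to CMR or to the primary endpoint. The within-arm sentence may simply serve the aim of describing mid-term change, for which paired tests are suitable. This is also a condensed article, and a full plan may hold more.

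Much of this stands, and it rules out several stronger readings.

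- A reader might infer that the follow-up data can never give a valid device comparison. The two-sample tests allow one, for 6-month PPR and for one-year quality of life.
- A reader might infer that quality of life, too, is claimed to give the more reliable comparison. The Discussion says this only of 6-month echocardiographic PPR.
- A reader might take 32–50% as this plan's error rate. No part of the article proposes to infer a device difference from one significant and one non-significant arm, and the within-arm powers are assumed.

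What the reply leaves open is differential change. The plan does not merely omit a method for change. It names one, and that method cannot answer the question the Discussion raises. A two-sample test of 6-month PPR does not answer it either.

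**Conclusion.** The point holds for the analysis of change. The stated within-arm tests cannot show whether PPR or quality of life changes differently between SAPIEN-3 and CoreValve, although the Abstract and Discussion put the follow-up data to between-device use. The available two-sample tests are valid for values at follow-up, but they are unadjusted and, for PPR, address a different question from differential change.

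The conclusion rests on reading the words about the arms as written, that is, with no arm factor in the ANOVA. If an arm factor was intended, the wording still needs correcting. The 32–50% range (9% with no change in either arm) is conditional: it applies only if a device difference is inferred from discordant within-arm results at the assumed powers.

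Only secondary endpoints are concerned. The primary CMR comparison at day 4 (+1) and the sample size are unaffected.

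**What to change.** Replace the sentence on change over time with between-arm analyses, before results are seen:

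- **PPR by TTE and by 3D TEE (within five days and at 6 months):** a repeated-measures model with arm, time and arm-by-time, on the log scale already chosen for regurgitation volume. Report the 6-month between-arm difference and the interaction, each with a confidence interval. Treat the early echocardiogram as an outcome and not as a covariate, because it is taken after implantation and already reflects the device.
- **KCC-Q, EQ-5D and SF-36:** the one-year between-arm difference adjusted for the baseline score of the same instrument.
- **Within-arm changes:** keep them, labelled as descriptive, and state that no device difference will be inferred from them.

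The cost is a few sentences of analysis text and standard models. No new visits, measurements or patients are needed. A mixed model can also include patients who have only one of the two echocardiograms, whom a paired test leaves out.

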### Sample size calculation

A sample size calculation for the primary endpoint post-TAVI PPR has been performed. A literature search on the difference in the extent of PPR after TAVI between the S3-THV and CV-THV prostheses has been done. No studies were found that included a quantitative PPR comparison between these two prostheses. We used data from 25 patients treated with TAVI at our centre for a sample size calculation. PPR quantification in these patients was performed using cardiac MRI. Because the distribution of these volume data was skewed to the right, we performed a log transformation on the original data to improve approximations to normality (original volumes presented as ml). The log transformed values were as follows: an overall mean regurgitant volume of 0.48, an ‘overall’ median regurgitant volume of 0.48, an overall standard deviation (SD) of 0.53, and a mean regurgitant volume of 0.32 for S3-THV and a mean regurgitant volume of 0.63 for CV-THV. CMR grades of PPR will be defined according to regurgitation fraction using similar reference cut-point values according to the standard grading criteria. As even mild PPR has been shown to be associated with long-term mortality, any significant difference in post-TAVI PPR volume between S3-THV and CV-THV is considered clinically important. The sample size calculation, including the above-mentioned log transformed values for mean regurgitant volumes and standard deviations, yielded a sample size of 49 patients in each arm to show superiority or equivalence over S3-THV and CV-THV with a power of 80%. As we took an expected dropout rate of 10% into account, this yielded a total sample size of 54 patients in each arm.

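### The 80% power claim covers equivalence, but the article states no equivalence margin or test, and the figures shown support 80% power for a difference only

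*Protocol article*

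**What the plan says.** The sample size section takes log-transformed cardiac MRI regurgitant volumes from 25 patients treated at the centre. It gives "a mean regurgitant volume of 0.32 for S3-THV and a mean regurgitant volume of 0.63 for CV-THV", with "an overall standard deviation (SD) of 0.53". The calculation is described as "including the above-mentioned log transformed values for mean regurgitant volumes and standard deviations", and it "yielded a sample size of 49 patients in each arm to show superiority or equivalence over S3-THV and CV-THV with a power of 80" percent. Allowing for 10% dropout, this becomes 54 per arm.

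The same section says that "any significant difference in post-TAVI PPR volume between S3-THV and CV-THV is considered clinically important".

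For the comparison of the valves, the statistical analysis section says that "log transformation will be performed on the regurgitation volume data before performing a *t* test". The significance rule is "A two-tailed *p*-value of less than 0.05 is regarded as statistically significant". The article gives no equivalence margin, no equivalence hypothesis and no confidence-interval rule for concluding equivalence. The sample size section is the only place where it mentions equivalence.

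**The concern.** Superiority and equivalence are different hypotheses. A test of superiority is sized on the difference one hopes to detect. A test of equivalence is sized on the largest difference one is willing to ignore. One sample size can serve both at 80% power, but only for a particular margin, and the article states none.

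The sentence that makes any significant difference clinically important deepens the problem. It names no size of regurgitation difference that could be disregarded, and a non-zero equivalence margin is exactly such a size.

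At stake is what the primary comparison can conclude. A reader told in advance that the trial has 80% power to show equivalence could take a non-significant t test as that demonstration. With 49 per arm, non-significance would not support it.

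**Working it through.** **Inputs.** From the sample size section: log means 0.32 and 0.63, so the difference is 0.63 − 0.32 = 0.31; SD 0.53; 49 per arm; power 80%. From the statistical analysis section: two-sided 0.05. The log base is not stated, so ratios are given for both bases. The margins in step 2 are assumptions.

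**Step 1. Reproduce 49 as a difference test.**

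Normal approximation: n = 2 × (1.96 + 0.8416)² × 0.53² / 0.31² = 45.9, so 46 per arm.

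Exact t test (noncentral t): 46.9, so 47 per arm. Power at 49 per arm is 81.8%.

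If the difference is rounded to 0.30, the normal formula gives exactly 49. The stated inputs are therefore consistent with a two-sided difference test at about 80% power.

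**Step 2. Equivalence power at 49 per arm.**

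SE = 0.53 × √(2/49) = 0.107.

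For margin m and true difference 0, two one-sided tests (TOST) have power of about Φ(m/SE − z) − Φ(−m/SE + z), set to 0 if negative. Here z is 1.645 for one-sided 0.05 and 1.96 for one-sided 0.025. The table uses t critical values (96 df), which lower the normal results by at most about 2 percentage points, except at 0.20 in the last column, where the normal formula gives 0%.

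| Assumed margin (log scale) | Power, one-sided 0.05 | Power, one-sided 0.025 |
|---|---|---|
| 0.155 (half of 0.31) | about 0% | 0% |
| 0.20 | 17% | 1% |
| 0.25 | 50% | 28% |
| 0.31 (all of the expected difference) | 78% | 64% |

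Example: at m = 0.31 and one-sided 0.05, m/SE = 2.895. The normal formula gives Φ(1.250) − Φ(−1.250) = 0.79, against 0.78 with t critical values.

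**Step 3. Smallest margin with 80% equivalence power at 49 per arm** (normal approximation, true difference 0).

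One-sided 0.05: 0.107 × (1.645 + 1.282) = 0.313.

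One-sided 0.025: 0.107 × (1.960 + 1.282) = 0.347.

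Both are at least the whole expected difference. On the volume scale, 0.31 is a ratio of 10^0.31 = 2.04 if log10, or e^0.31 = 1.36 if natural log.

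These figures need a true difference of exactly 0. With a true difference of 0.10 and a margin of 0.31, power falls to about 60% at one-sided 0.05.

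**Step 4. What non-significance would leave open.**

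The 95% confidence interval half-width is 1.985 × 0.107 = 0.21. A result that just misses significance has an observed difference near 0.21 and an interval from about 0 to about 0.43. The upper end is a volume ratio of about 2.7 (log10) or 1.5 (natural log). That interval contains the full difference of 0.31 the trial was sized on.

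**The case against.** The strongest objection is that TOST can also produce a number near 49. A margin of 0.31 at one-sided 0.05 needs 51 per arm, and the difference test needs 47, so each is two patients away. The article does not name the test used for sizing. A reader might infer that 49 was derived from a difference test alone, but the documents do not establish this. They show only that the inputs fit one.

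A reader might also infer that no margin exists anywhere. The full protocol and the analysis plan are not shown, so what can be said is that the article states none. Leaving a margin to a fuller document would be unremarkable by itself. The fault lies in what is printed: a power for equivalence beside a sentence that conflicts with any non-zero margin.

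Third, a reader might infer that the investigators intend to report a non-significant result as equivalence. Nothing in the article says so. The stated aim is to look for differences, and the discussion makes no equivalence claim. The risk comes from the wording of the power statement, not from a declared plan.

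It is also fair that 0.155, 0.20 and 0.25 have no basis in the article, and that margins above 0.31 do give 80% or more (0.32 gives 81% at one-sided 0.05). Nor does the article set 0.31 as a threshold of importance; it is the difference between the centre's own arm means. What survives is narrower: reaching 80% requires a margin at least as large as the difference the trial was sized to detect.

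**Conclusion.** The power statement is wrong as written. The figures support about 80% power for a difference (81.8% at 49 per arm, two-sided 0.05, difference 0.31, SD 0.53). They do not support 80% power for equivalence, which is undefined without a margin. Under the assumed margins in the working, with a true difference of 0, equivalence power at 49 per arm runs from about 0% to 78% at one-sided 0.05, and is 64% at 0.31 with one-sided 0.025. All of this rests on the article's SD of 0.53 and on 49 evaluable patients per arm.

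The point is limited to that claim. The sample size for the difference test and the planned t test are not called into question.

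**What to change.** In the sample size section, delete the words *or equivalence* and restate the claim as 80% power to detect a difference: two-sided 0.05, difference 0.31 on the log scale, SD 0.53. Add that a non-significant result will not be interpreted as equivalence but through the 95% confidence interval of the difference, back-transformed to a ratio of geometric mean regurgitant volumes. Name the log base so that the ratio can be read.

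The cost is one or two sentences and a less favourable stated claim, with no extra patients.

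If equivalence is truly an aim, deletion is not enough. A justified margin, a TOST or confidence-interval rule and a sample size for that margin must then be stated, and the sentence on any significant difference reconciled with the margin. A per-protocol analysis should then be added, because the article says that "All analyses will be performed according to the intention-to-treat principle". That route could cost patients: an assumed margin of 0.155 would need about 201 per arm at one-sided 0.05, and 0.20 would need 121 (normal approximation, 80% power, true difference 0).

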## Discussion

The ELECT trial is the first randomised controlled trial to quantitatively compare the magnitude of post-procedural PPR between the S3-THV prosthesis and CV-THV. Other important objectives of this trial include assessment of the value of angiography, transthoracic and (3D) transoesophageal echocardiography and cardiac MRI for the measurement of post-TAVI PPR severity.

Regardless of the prosthesis type, post-procedural PPR is a common complication after TAVI associated with increased mortality [17]. A meta-analysis [25] including 45 studies reported an overall incidence of moderate or severe PPR of 11.7% within 30 days after TAVI. The balloon-expandable S3-THV [24] and self-expanding CV-THV [31] are two transcatheter heart valves that are in widespread use worldwide. Few previous studies comparing the haemodynamic performance of these two types of prosthesis have suggested a higher incidence of moderate or severe post-TAVI PPR accompanying the implantation of CV-THV [1, 25].

An important aspect of CV-THV that might increase the risk of post-TAVI PPR (and thus explain the aforementioned data) is the intrinsic radial strength of its nitinol frame, which may not be sufficient for complete apposition of the prosthesis to the native annulus. This incomplete apposition might create periprosthetic gaps, especially in the presence of calcification along the aortic wall. Furthermore, an extreme angulation between the left ventricular outflow tract and the ascending aorta (also called the horizontal aorta) may reduce the ability of the CV-THV prosthesis to seal the paravalvular space [25]. Therefore, oversizing and balloon post-dilatation are more important in CV-THV implantation than in S3-THV implantation. In addition, owing to the non-cylindrical shape of the CV-THV system, its effective area inside the aortic annulus depends on the depth of the prosthesis in the left ventricular outflow tract. Therefore, in the CV-THV the sealing of the paravalvular space by the prosthesis also depends on the depth of its implantation. However, besides the factors mentioned above, which make CV-THV susceptible to post-TAVI PPR, we also need to keep in mind that the self-expanding nitinol frame has the potential to further expand over time. Therefore, the apposition of the prosthesis frame to the aortic annulus has the potential to improve gradually, decreasing the extent of post-TAVI PPR with passage of time.

Interestingly, the recently published results of the CoreValve US Pivotal Trial [32] showed that the incidence of any PPR after the implantation of CV-THV decreases over time: 41.1% at discharge and 31.9% at one year. The latter was also accompanied by a reduction in the incidence of more-than-mild aortic regurgitation during follow-up, at 13.8% at discharge, 10.1% at 6 months, and 6.4% at one year. This suggests that measurement of post-TAVI PPR in the CV-THV during the few first days after TAVI will probably overestimate its long-term severity. In the ELECT study, the severity of PPR is also measured at 6‑month follow-up using transthoracic and 3D transoesophageal echocardiography, which allows for a more reliable comparison between the two prostheses.

One previously published meta-analysis [25] showed a higher risk of moderate or severe post-procedural PPR after CV-THV implantation (16%) as compared with E﻿d﻿w﻿a﻿r﻿d﻿s SAPIEN implantation (9.1%, *p* = 0.005). The CHOICE study [18], which is the only randomised head-to-head trial to date that has compared the balloon-expandable SXT-THV with the CV-THV system, reported a significant difference in the frequency of any degree of PPR (38% in SXT group versus 65% in the CV group, *p* < 0.001) and more-than-mild PPR (4.1% in SXT group versus 18.3% in the CV group, *p* < 0.001 by angiography) favouring the balloon-expandable valve. However, the extent of the PPR in the CHOICE trial was measured using aortic root angiography immediately after prosthesis implantation, which is an important limitation of this clinical trial.

On the other hand, the PRAGMATIC [33] study reported a very low and comparable incidence of more-than-mild PPR with both Edwards SAPIEN and CV-THV (1.8% and 2.0%, respectively) in a large multicentre propensity score-matched study. Recently, another study among a selected group of patients receiving S3-THV or CV-THV reported a significantly lower rate of mild or severe PPR, lower need for permanent pacemaker implantation, and higher rate of device success for the S3-THV compared with CV-THV. However, this study was limited by its design and small sample size [34].

Obviously, there is a discrepancy in the incidence of PPR across different studies that is most probably related to the challenges in identification and quantification of post-TAVI PPR. Also, the VARC-2 document [29] did not propose new diagnostic criteria for adequate assessment of post-TAVI PPR. The lack of a standardised and validated method for evaluation of post-TAVI PPR is a major limitation in comparing echocardiographic PPR analysis performed in different studies and meta-analyses. Aortic regurgitation after TAVI usually consists of multiple eccentric jets that are non-parallel and irregular in shape [21, 35].

Eccentric jets are frequently entrained along the left ventricular wall with fanning of jets as they regurgitate. Therefore, the eccentric aspects of post-TAVI PPR make the assessment of its severity challenging. Also acoustic shadowing from the calcifications and Doppler attenuation from the prosthesis can obscure regurgitant jets and thus result in underestimation of their severity [35].

On the other hand, assessment of PPR severity using aortic root angiography relies on subjective assessment of unidimensional images, and can be affected by inter-observer and intra-observer variability.

In the ELECT trial, the severity of PPR is measured quantitatively using several different modalities, from dedicated software for angiography [23] directly post-TAVI implantation to either transthoracic and transoesophageal echocardiography (with 3D reconstruction) [20, 21] to cardiac MRI including phase contrast sequences [22]. The main focus of the ELECT trial will be the comparison of the different imaging modalities in assessing PPR, using CMR as a primary endpoint. This comparison is an important aspect of the present trial as to date there is no validated tool for reliable measurement of post-TAVI PPR.
